## Abstract

**Background:**

Chronic pain in older people is highly prevalent, often underestimated, and associated with adverse outcomes. Most available analgesic drugs are often either ineffective or not tolerated, with many side effects. Palmitoylethanolamide (PEA) is an endogenous widely distributed *N*-acylethanolamina involved in neuroinflammation and pain-generating processes. Formulations containing ultra-micronized palmitoylethanolamide (um-PEA) are available but their effectiveness on chronic pain in highly heterogeneous geriatric patients is not clear and probably not generalizable. We planned to adopt the *N*-of-1 trial approach to test the effectiveness of um-PEA objectively at the individual level in our older outpatients.

**Methods/Design:**

Persons 65 years or older referring to the Geriatric Unit of the Fondazione IRCCS Ca’ Granda Ospedale Maggiore Policlinico of Milan complaining of noncancer chronic pain of any origin will be eligible. Each trial will be a placebo-controlled randomized crossover trial including two um-PEA (600 mg twice a day) and placebo treatment pairs. The um-PEA or placebo 3-week periods will be separated by 2-week washout intervals to overcome possible carryover effects. Pain intensity, need of on-demand analgesic medications, and impact on daily activities will be evaluated. Cognitively impaired patients will be eligible as long as an expression of pain can be recognized and its frequency assessed by a caregiver. Trial results will be discussed with the patient or caregiver and the treating physician to decide whether to continue the treatment. The impact of the *N*-of-1 approach on the physician’s management plan and confidence will be assessed. We will secondarily meta-analyze the performed *N*-of-1 trials to obtain an estimate of the average effect of um-PEA compared with placebo using a frequentist and Bayesian approach.

**Discussion:**

While pursuing an ultimate clinical objective, i.e. to empirically and objectively decide the best treatment choice for an individual older patient with chronic pain, these series of geriatric *N*-of-1 trials on PEA will bring the principles of evidence-based medicine into the care of patients not usually represented in conventional randomized controlled trials, and realize a patient-centered outcome approach necessary to improve appropriate prescribing in elderly patients with multimorbidity and polypharmacy.

**Trial registration:**

ClinicalTrials.gov NCT02699281. Registered on 3 March 2016.

**Electronic supplementary material:**

The online version of this article (doi:10.1186/s13063-016-1496-9) contains supplementary material, which is available to authorized users.

## Background

Pain prevalence increases with age. In particular, the prevalence of chronic or persistent pain among older people ranges from 45 % to 80 % [1]. Persistent pain is a frequent reason for physician office visits among older persons [2], with women being more likely to report persistent pain than men [3]. Among older adults, the most frequent noncancer pain complaints are osteoarthritic back pain, especially in the low back or neck (around 65 %), musculoskeletal pain (around 40 %), peripheral neuropathic pain (typically due to diabetes or post-herpetic neuralgia, 35 %) and chronic joint pain (15 %–25 %) [4–6]. In fact, persistent pain may or may not be associated with a well-defined disease process [7].

Persistent pain and its inadequate treatment are associated with adverse outcomes in older people: functional impairment, falls, slow rehabilitation, mood changes, and sleep and appetite disturbances, resulting in a higher consumption of healthcare resources [8].

Achieving pain control in geriatric patients is complicated by many issues. First, older people may underreport pain, and in this population persistent pain has often complex and multifactorial manifestations. Self-reporting is deemed to be the gold standard in pain assessment but older people might find difficult to complete self-reported questionnaires of pain and functional status, developed and validated in younger patients [7, 9]. Pain evaluation is particularly cumbersome in older patients affected by dementia, who can express pain through unusual verbal and non-verbal modalities. Facial expression, verbalizations, non-verbal sounds, body movements, variations in interpersonal relationships, and mental status changes might be pain manifestations, and should be taken into account in pain evaluation even if extremely non-specific [1].

Second, the somatosensory system changes with aging [10], through the alteration or loss of myelinated and unmyelinated nerve fibres [11], an impairment in the endogenous opioid and non-opioid inhibitory systems of pain modulation [12], and a modified neuroplasticity [13]. All these changes lead to a reduced pain threshold, dysfunctional pain signaling, hyperalgesia, and central sensitization.

Third, pharmacological management of chronic pain is particularly challenging in the elderly. Owing to age-related body changes affecting drug pharmacokinetics, and because of multimorbidity and polypharmacy, older patients are generally more likely to experience drug-related adverse effects [7]. In particular, safety concerns can arise with most of the available analgesic drug classes. Given a better safety profile than traditional nonsteroidal anti-inflammatory drugs, acetaminophen is usually indicated as first line therapy for pain [7]. However, concerns about its efficacy on low back pain and osteoarthritis of the hip or knee, and about its actual safety, especially at the upper end of standard analgesic doses, have been raised by two recent systematic reviews of, respectively, randomized placebo-controlled trials [14] and observational studies [15]. Nonsteroidal anti-inflammatory drugs are more effective in the treatment of chronic inflammatory pain, but are burdened with many side effects, such as gastrointestinal bleeding, renal injury, and cardiovascular toxicity, which increase in frequency and severity with age [16, 17]. These safety issues are only partially mitigated with cyclooxygenase-2 selective inhibitors [18, 19]. Although their potential efficacy on persistent noncancer pain has been proved in some controlled trials, the adverse effects associated with opioids represent a barrier to their adoption and a frequent reason of drug discontinuation [20, 21]. In addition to other usual adverse effects, such as constipation and nausea, a negative impact on vigilance and cognitive performance is common in older persons. Newly prescribed opioid treatment has been associated with a higher risk of falls [22], so that the 2015 update of Beers criteria on potentially inappropriate medication use in older adults included it among the considerations on disease and syndrome interactions [23]. Although tolerance to central respiratory depression develops quickly, rapid dose increase, drug–drug interaction with other central nervous system depressants, and drug accumulation or accidental overdose are potential determinants of respiratory failure onset during opioid treatment [24].

So called adjuvant (or pain-modulating) drugs, co-administered with other analgesics, have been found to be effective in attenuating pain perception, particularly in the treatment of neuropathic pain [7]. They include antidepressants, anticonvulsants (e.g. pregabalin and gabapentin) and other medications that alter neural membrane potentials, ion channels, cell surface receptor sites, synaptic neurotransmitter levels, and other neuronal processes involved in pain signal processing. To minimize their potential adverse effects, these central nervous system drugs must be carefully titrated and monitored frequently [7].

All pain-modulating therapies target neurons, the principal component of the pain unit. However, a growing body of evidence suggests that immune cells, in particular mast cells and microglia, play a substantial role in the somatosensory system, being the primary interlocutors for pain neurons, both in the periphery and at the spinal and supraspinal levels [25]. Immune cells are located in proximity to sensory nerve endings and vasculature. After an injury or in the presence of an inflammatory stimulus, immune cells release mediators, such as bradykinin, prostaglandins, and histamine, stimulating nociceptors and playing an important role in the induction, amplification, and maintenance of chronic pain [26]. Physiological activation of microglia generally leads to resolution of neuroinflammation and restoration of tissue homeostasis. With aging, both microglia and mast cells increase their reactivity with a more intense response to a stimulus and a more robust production of pro-inflammatory cytokines lasting for an extended period [27, 28]. All these findings support the hypothesis that non-neuronal cells might be important therapeutic targets for the treatment of chronic pain, especially in older persons.

Palmitoylethanolamide (PEA) is an endogenous *N*-acylethanolamina widely distributed in different tissues [29]. It is synthesized on demand and its levels vary after stress or injuries, like those associated with pain [30]. In murine models of chronic inflammation and chronic or neuropathic pain, PEA seems to be able to reduce the recruitment and activation of mast cells, the production of pro-inflammatory mediators, and endoneural edema, thus reducing both pain and inflammation while preserving peripheral nerve morphology [31, 32]. Micronized or ultra-micronized PEA (m- and um-PEA) is available in Italy as an active molecule in several products classified as ‘Food for Special Medical Purposes’ (European Commission Directive 1999/21/EC), indicated for use ‘under medical supervision’ to treat conditions whose pathogenesis involves neuroinflammation. Evidence on the efficacy and safety of PEA in the treatment of chronic or neuropathic pain, alone or as add-on therapy, published as full articles or conference abstracts, in peer-reviewed or non-peer-reviewed journals, is currently based mostly on observational studies and case series, and on a few double-blind or open label randomized controlled trials [33–37]. Recently, in a meta-analysis of published and unpublished data, Paladini *et al*. [38] confirmed the efficacy of PEA on pain intensity independently of sex, age, and type of pain, even if with a smaller effect in people older than 65 years. Serious product-related adverse events were not reported in any of the included studies.

The mechanism of action and the safety profile make PEA an appealing choice for pain relief in older people. However, the evidence base for its efficacy to treat chronic pain in the elderly is not fully convincing. In addition, formulations containing um-PEA, like *Normast®*, are available in Italy only out-of-pocket and a treatment cycle at the doses recommended by the product information sheet would cost the patient about € 60. Given that the required treatment for persistent pain would probably be longer, the cost should be balanced by the actual effectiveness. These reasons represented the rationale to adopt a randomized *N*-of-1 trial as a more objective and personalized prescribing approach, compared with the conventional trial (i.e. ‘prescribe and see’) [39]. In general, *N*-of-1 trials are within-patient randomized multi-period crossover trials to compare, in a double-blind fashion, therapeutic strategies (e.g. an active drug versus no treatments, or two different active therapies), with time periods as randomization units and the patient as control for herself or himself. This study design can be theoretically used to test new drugs along their way to marketing authorization. In our case, we will adopt this approach to determine the best therapeutic choice for a certain patient in clinical practice, objectively and empirically, with randomization and blindness as instruments to overcome those factors (e.g. natural history of the disease, ‘placebo effect’, expectations) that might bias conventional trials of therapies [39–41]. In particular, the series of *N*-of-1 trials on PEA for chronic pain in older patients will be part of the activity of the Geriatric *N*-of-1 Service, an experimental project that we have implemented, with the approval of the local ethical committee, following the pioneering experience of Guyatt and colleagues [42] but in the specific context of geriatric medicine, which suffers most from the limits of parallel group randomized controlled trials, the current paradigms of evidence-based medicine [43].

## Methods/Design

This study protocol has been realized according to the CONSORT extension for reporting N-of-1 trials (CENT) 2015 [44] and the SPIRIT statements. The SPIRIT and CENT checklists for our paper are provided as Additional files 1 and 2, respectively.

### Study objectives

The primary (clinical) objective of our study is to apply the *N*-of-1 trial approach to test the effectiveness of um-PEA 600 mg (*Normast®*) twice a day for chronic pain in a certain patient referring to our geriatric unit in whom the treatment might be indicated, and to assist decisions on long-term treatment of that patient.

As a secondary (research) objective, we aim to obtain an overall estimate of the effectiveness of um-PEA 600 mg twice a day compared with placebo and evaluate the possible determinants of between-trial heterogeneity, through a meta-analysis of the *N*-of-1 trials performed for clinical purposes. Contextually, a classical frequentist meta-analytical approach will be compared with a Bayesian approach, and the potentialities of a Bayesian-based cumulative study design explored.

### Study design

Each trial will be a blinded placebo-controlled randomized trial. Each trial’s duration will be 18 weeks, comprising two um-PEA and placebo treatment pairs assigned in a random order according to a pairwise randomization scheme. Thus, the sequence of each pair can be either um-PEA/placebo or placebo/um-PEA. Each treatment period will last 3 weeks. The treatment periods of each pair and the two pairs will be separated by 2-week washout intervals to minimize carryover effects. A run-in period will not be routinely performed, but will be considered when deemed appropriate (for example, in case of history of allergies to drugs or drug excipients). Figure 1 summarizes the schedule for the intervention and washout periods.

**Fig. 1 Fig1:**
[figure not shown]
SPIRIT Study diagram. *W*
_*n*_: week number, D: daily W: weekly. The study duration is 18 weeks. After the baseline assessment at time 0, patients will have two pairs of active drug (3 weeks) and placebo (3 weeks) exposures. Randomly assigned treatment pairs will comprise two treatment periods (active therapy or placebo) separated by a 2-week washout period. Treatment pairs will also be separated by washout periods

This study design was conceived taking into account the available information on the product pharmacological characteristics, balanced with the need for a trial with an acceptable duration from the practical viewpoint. The onset time of PEA is not easily predictable from its pharmacokinetics or pharmacodynamics. According to the available literature, most people notice the effects within 1 week, but sometimes 6–8 weeks are required, especially for chronic pain syndromes. Regarding a possible carryover effect, no sufficient data are currently available, either from basic or clinical research studies, to make a definitive statement. However, given the type of mechanism of action, a possible residual effect might be expected. Concerning the dose, in the heterogeneous literature on the use of the product for pain control, different doses have been tested, from 300 mg a day to 2400 mg a day, either once or split into three doses per day. The product information sheet for Normast® 600 mg suggests ‘1–2 tablets a day for 20–30 days’.

#### Eligibility criteria for participants

Older patients complaining of chronic pain of likely osteoarticular or neuropathic origin will be eligible for the study. Detailed *inclusion criteria* are:Patient age ≥ 65 years.Pain is localized at the back (any level) or at the joints or at the limbs.The pain is chronic, i.e. it has been present for at least 6 months, even if with fluctuations.The pain is attributable to one or more of the following conditions: osteoarthritis or osteoarthrosis; spondylosis; radiculopathy; diabetic peripheral neuropathy; post-herpetic neuralgia; chronic idiopathic axonal polyneuropathy; fibromyalgia; or pain of uncertain origin or idiopathic, as long as it has had and it is expected to have a chronic nature, even if with spontaneous fluctuations.The treating physician deems PEA to be a possible treatment option for the patient, either alone or as an add-on medication on top of other analgesic drugs.

Dealing with geriatric patients, and willing to offer the opportunity of a treatment option with an objective and empirical evaluation regardless of patient cognitive integrity, we will distinguish two cases:Case 1 (self-assessment): The patient is able to give an informed consent and to express the characteristics of the pain-like intensity and impact on function over a quantitative scale; the patient might be able to self-compile questionnaires, or to reliably answer questions administered by a caregiver.Case 2 (caregiver-based-assessment): The patient has a certain degree of cognitive decline that hinders the direct involvement of the patient in the consent process or in the outcome self-assessment, but an all-day caregiver willing to collaborate and consent to the trial is present. In this case, the pain has to be clearly expressed by the patient in a modality that can be assessed in its frequency and impact on function by someone other than the patient.

*N*-of-1 trials on case 1 patients will be candidates for the secondary objective of our study. The opportunity to meta-analyze case 2 trials will be judged according to the number and heterogeneity of the assessment instruments and modalities of completed trials.

Patients with cancer-related pain and patients with a clear ischemic pathogenesis for pain (e.g. intermittent claudication or critical limb ischemia) will be excluded. There will be no exclusion criteria concerning the comorbidities the patient might have. Patients can take other medications or undergo non-pharmacological therapies (e.g. physical therapies) for chronic pain control as long as they are not newly commenced; generally, no therapy modification that can affect pain must have been made soon before or concomitantly with the enrollment in the *N*-of-1 trial.

#### Setting and recruitment

The study will be conducted at the Geriatric Unit of the Fondazione IRCCS Ca’ Granda – Ospedale Maggiore Policlinico in Milan, Italy, which is an academic tertiary hospital unit that serves inpatient and outpatient referrals.

Patients will be mainly recruited from the geriatric outpatient clinic. Referrals might also be generated in the inpatient clinic but, to be enrolled in the study, patients need to have recovered from any acute illness.

### Interventions

One tablet containing either *Normast®* 600 mg or placebo will be administered orally twice daily during the treatment periods. No study drug will be administered during the washout period.

The patient will be allowed to take on-demand painkillers during the entire trial duration. At the baseline visit, the patient will be recommended according to our usual geriatric practice, i.e. to take acetaminophen at a maximum dose of 2 g daily if not contraindicated or in case of drug allergy or intolerance; if acetaminophen is insufficient, to combine or replace it with codeine or tramadol; to use ibuprofen when pain is not eventually controlled, trying to avoid, in general, nonsteroidal anti-inflammatory drugs. The patient will be given instructions on how to report on-demand analgesia according to the outcome assessment instruments and modalities.

### Outcome measures

Outcome measures evaluated in each *N*-of-1 trial will be the daily intensity of pain, the daily need of on-demand analgesic medications, and the impact of pain on daily activities measured over a week time (case 1: self-assessment trials).

In the cases in which self-assessment is not feasible (case 2: caregiver-based assessment trials) the daily frequency with which the patient complains of pain measured by the patient’s caregiver will be adopted as the outcome measure, since the measurement of the frequency of pain complaints by someone other than the patient is expected to be more feasible than the quantification of pain intensity. The daily need of on-demand analgesic medications and the impact of pain on daily activities over a week will also be evaluated in case 2 trials.

For the purpose of deciding for the optimal treatment in the patient, all the listed outcome measures will be valued. For meta-analytical purposes, the daily intensity of pain (case 1) or the daily frequency of pain symptoms (case 2) will be the *primary outcome measure*; the daily need of on-demand analgesic medications, and the impact of pain on daily activities will be the *secondary outcome measures*.

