### Participant timeline

The study timeline is reported in Fig. 1.

At the enrollment visit, eligibility criteria will be checked, informed consent will be obtained, and data regarding patient socio-demographics, pain characteristics, comorbidities, and pharmacotherapy will be collected. The clinical investigators will also evaluate the ability of the patient and the caregiver to assess pain intensity, and appropriate training for questionnaire fulfilment will be performed.

After allocation, the study drug will be delivered to the patient (case 1) or caregiver (case 2) and baseline pain intensity and functional status will be recorded.

The patient or caregiver will be contacted by telephone after the first week of treatment to investigate possible issues concerning therapeutic adherence, adverse effects, and questionnaire completion. A visit with the patient and caregiver will be scheduled before the beginning of each period, to deliver the study drug and acquire the completed questionnaires, checking their correct fulfilment. At the end of the last period, the last questionnaires will be collected.

A final visit with the patient will be scheduled at the end of the trial, once the study results are available. The patient, the caregiver, the treating physician, and the study investigators will discuss the study results.

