### Monitoring

Owing to the small amount of data to be managed and to the absence of funding, a data monitoring committee is not recruited. Data will be managed and monitored directly by the study investigators. The correct use of the study drug and instruments, and possible adverse effects will be monitored at each phone or in person contact with the patient. Patients will be encouraged to report any possible adverse effect or concern about the study for the whole study duration through the provided investigators’ phone contacts.

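### Adverse effects are collected while everyone is blinded, but no stated step brings them into the masked A/B comparison that guides long-term um-PEA use

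*Protocol article*

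**What the plan says.** The Study objectives section makes the individual trial the primary purpose, including "to assist decisions on long-term treatment of that patient".

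The Outcome measures section gives the list for self-assessed patients (case 1), whose third domain is function: "Outcome measures evaluated in each *N*-of-1 trial will be the daily intensity of pain, the daily need of on-demand analgesic medications, and the impact". For caregiver-assessed patients (case 2), frequency of pain complaints replaces intensity, and the other two domains stay: "The daily need of on-demand analgesic medications and the impact of pain on daily activities over a week will also be evaluated in case 2". The section then ties the clinical decision to the list: "For the purpose of deciding for the optimal treatment in the patient, all the listed outcome measures will be valued".

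Under Analysis of individual N-of-1 trials, the result is a cross-tabulation and graph of week and period mean pain scores by treatment, with a similar synthesis for function. Physician and patient or caregiver judge it as A versus B before the code is broken.

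Adverse effects appear elsewhere. The Monitoring section says "possible adverse effects will be monitored at each phone or in person contact with the patient", and adds a patient-initiated route: "Patients will be encouraged to report any possible adverse effect or concern about the study for the whole study duration". The Participant timeline places a telephone call after the first week of treatment and a visit before each period, and says of the end: "At the end of the last period, the last questionnaires will be collected". The Allocation and blinding section allows a trial to be concluded for safety concerns.

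**The concern.** The decision at the end of each trial is whether this patient should stay on um-PEA. The protocol's own Background gives poor tolerability of other analgesics, and the safety profile of PEA, as reasons for considering the product. One would therefore expect tolerability to be among the things compared between A and B.

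As written, a patient with a modest score gain on one treatment and a recurrent unwanted symptom on that same treatment would be shown a table that favours it, with nothing in the table to set against the gain. The masked reading exists to keep expectation out of the judgement. If tolerability is weighed outside the masked table, and possibly only once the code is known, that part of the decision lacks the same protection. Harm enters the classification of results (Evaluation of N-of-1 trials on PEA) only as the direction of a significant mean difference, and the paired test is specified for period mean scores.

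**Working it through.** **Step 1. Reproduce the schedule.** Inputs from Study design: four treatment periods of 3 weeks and three washouts of 2 weeks.

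4 × 3 + 3 × 2 = 12 + 6 = 18 weeks, which matches the stated duration. Periods run over weeks 0–3, 5–8, 10–13 and 15–18.

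**Step 2. Place the contacts.** From Participant timeline: a visit before each period (weeks 0, 5, 10, 15), one call after the first treatment week (week 1), and questionnaire collection at the end of the last period (week 18, taken here as a contact).

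- Contacts: weeks 0, 1, 5, 10, 15, 18.
- Gaps: 1, 4, 5, 5 and 3 weeks.
- Contacts after dosing begins: 5.
- If the call is read as once per period, contacts fall at weeks 0, 1, 5, 6, 10, 11, 15, 16 and 18. The longest gap is then 4 weeks, with 8 contacts after dosing begins.

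The final results visit is additional, but its timing is not stated.

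**Step 3. Compare with the listed measures.** Pain is recorded daily: 18 × 7 = 126 days, of which 4 × 3 × 7 = 84 are treatment days. Function is recorded at baseline and weekly: 18 + 1 = 19 assessments. The individual-trial analysis refers to measures made during washouts, so the daily sheet is in use there too.

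**Step 4. Can an event be linked to a treatment?** Each visit precedes the next period, so the intervals 0–5, 5–10 and 10–15 each hold one treatment (3 weeks) and its washout (2 weeks), and 15–18 holds the fourth treatment. Every interval maps to one treatment, and the pharmacist's record supplies which.

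**Step 5. Follow adverse effects to the decision.**

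| Step in the protocol article | Adverse effects included? |
|---|---|
| Outcome measures, case 1 and case 2 | No |
| Daily and weekly instruments, as described in the text | No |
| Individual-trial cross-tabulation and graph | No |
| Masked A/B reading | Not in the described result |
| Monitoring at contacts and by patient telephone report | Yes, not linked to the A/B result |
| Conclusion of a trial for safety concerns | Yes, but this ends the trial |

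The information is collected, and can be attributed to a treatment, but no described step carries it into the A/B comparison.

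**The case against.** The strongest reply is that tolerability is handled. Adverse effects are sought at every contact, patients may telephone throughout, safety concerns can conclude a trial, and the final discussion bars no topic. The sentence on valued measures does not say that only these count, and it is followed by a ranking of outcomes for meta-analysis, so it may be meant only as a contrast. Adverse-effect forms and summaries are often left to a full protocol. Figures 1 to 3 and the reporting checklists are not shown, so an adverse-effect field on a form cannot be excluded.

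Much of this stands, and it rules out several stronger readings that a reader might infer:

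- *That harm would be known only from undated recollection.* The telephone route lets events be reported, and dated, as they occur.
- *That the washout share of each 5-week interval (2/5 = 40%) prevents attribution.* Each interval holds a single treatment, so attribution to a treatment is possible; only separation of dosing from washout days is blurred.
- *That the pooled series cannot compare tolerability with placebo.* Intervals can be linked to the recorded allocation, so it can.
- *That adverse effects are gathered unblinded.* Patients, caregivers, treating physicians and investigators are blinded while the contacts take place.
- *That shorter follow-up after period 4 biases the series.* Within a patient, the treatment given last has 2 washout weeks and the other has 4. Which comes last is randomised, so neither is favoured systematically. The Study design remark that "given the type of mechanism of action, a possible residual effect might be expected" concerns carryover and makes no statement about delayed adverse effects.

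The reply does not remove the central point. The article does more than stay silent on safety forms: it states which measures are valued for the decision and what the masked result contains, and tolerability is in neither.

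**Conclusion.** The point holds in a limited form. Adverse effects are monitored, but they are absent from the stated decision measures (three domains, in both cases) and from the described masked A/B result. Solicited enquiry takes place up to 5 weeks apart as described, or up to 4 weeks if the call is made in every period, while pain is recorded daily. The blinded comparison behind a long-term treatment decision therefore has no specified tolerability component.

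This is a gap in how the result is assembled, not a failure to monitor safety and not an internal contradiction. Its effect on decisions cannot be sized, because the documents give no adverse-effect rate for either treatment. The conclusion assumes that the unseen figures contain no adverse-effect field; the text and captions describe none. If the daily sheet already has one, the diary line is unnecessary, but the additions to the decision measures and the masked table would still be needed. The change is worth making because it is cheap and uses forms and blinding already in place.

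**What to change.** 1. Add adverse effects to the measures valued for the individual decision in Outcome measures, for both cases.
2. Add one line to the existing daily sheet: any new or worse symptom today (yes/no, what). The caregiver completes it in case 2.
3. In Analysis of individual N-of-1 trials, tabulate adverse effects by period, counting each treatment with its following washout, under the labels A and B. Show this table with the pain and function results before the code is broken.
4. Summarise adverse effects by treatment in the pooled report.

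Continuing the diary for 2 weeks after period 4 is optional. It would even out follow-up within a patient, at the price of a results discussion about 2 weeks later.

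The cost of items 1 to 4 is slight extra diary burden, one more row in the masked table, and some non-specific symptom reports, which are to be expected in older patients with several conditions and should be read against the placebo periods.
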